## Study protocol

Study design, duration and setting – This will be a prospective one group cohort study for a period of twelve months which will be based in Ibrahim Hyderi, a peri-urban settlement of approximately 70,000 on the south east of Karachi. It is one of the seven union councils in Bin Qasim town which has a population of one million. A primary health care clinic (PHC) run by the Department of Peadiatrics and Child Health, The Aga Khan University (AKU) provides free care of early childhood illnesses and pregnancy services including antenatal checkups and free ultrasound. Pregnant women self-refer for basic ultrasound and antenatal follow-ups.

Study subjects and eligibility criteria- Pregnant women between 22–34 weeks who reside in Ibrahim Hyderi Goth. This site was chosen for their static population and the presence of demographic surveillance system setup by the Department of Pediatrics and Child Health, Aga Khan University for several years. The presence of this system ensures that women can be tracked during pregnancy and after delivery to ascertain their outcomes, which is critical to this project. This gestational age is most feasible to perform fetal Doppler that may help predict adverse outcomes. The eligibility criteria of the study are as follows:

Inclusion criteria:

• Pregnant woman coming to the ultrasound clinic between 22–34 weeks of gestation.• Written informed consent obtained• Resident of the study area

Exclusion criteria:

• Multiple gestation• Known congenital anomaly in the fetus or newborn• Refusal for the ultrasound• Poor echocardiographic images for Doppler acquisition

Outcomes –

The primary outcomes of this study include:

• Stillbirth (baby born with no signs of life at or after 28 weeks of gestation) and• Early neonatal mortality (death of a baby within the first 7 days of life).

The secondary outcomes include:

• IUGR – Fetal weight that is below the 10
^th^ centile for gestational age on ultrasound• Prematurity – Birth of a fetus < 37 weeks of gestation• LBW – Birth weight < 2.5 kg• Birth asphyxia – Delayed cry after at least 1 minute of life• Early neonatal sepsis – Any 1 of the following signs: fever > 38 or < 35 Celsius, convulsions, lethargy, poor feeding, chest in drawing and tachypnea (respiratory rate > 60 breaths per minute) within 7 days of life
^9^

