Sample size estimation – The sample size is based on outcomes of the pregnancies and not based on etiology of outcome. For the training of the machine learning, as much data as possible is required and this would be typically in the order of magnitude of thousands of patients. Given that this is not feasible in the pilot study, the training data will be mainly synthetically generated through a computational model of the fetal circulation. This allows the generation of thousands of 'individuals'. A recent randomized clinical trial conducted on machine learning in heart failure with 1106 patients with 20% having an adverse primary outcome and 5 different phenotypes, it was seen that above a sample size of 500 patients, the learned information becomes stable and doesn't change much
^10^. Additionally, we will be using socio-demographic, and pregnancy and labor characteristics, along with the Doppler, where the combined analysis should make the detection additionally more robust.

In the study area there are 30 stillbirths per 1000 total births while there are 30 neonatal deaths per 1000 live births. If 500 pregnant women are to be enrolled in the study duration, we expect to find approximately 25–30 adverse perinatal outcomes. To account for loss to follow up, we will inflate the sample size by 5% and enroll 525 pregnant women. Sample size was estimated from experience with the proposed machine learning approach, where stability of the learning phase was reached around 500 included patients
^18^, combined with the fact that data augmentation of the training set will be performed using the previously validated computational model of the fetal circulation
^7^.

Recruitment – Household surveillance will be done by community health workers (CHWs) in the catchment area in a sequential manner to identify pregnant women. Eligible women between 22–34 weeks of gestation on last menstrual period (LMP) will then have the purpose of the study explained to them and be invited for an ultrasound scan. At the clinic, all inclusion/exclusion criteria will be assessed. All screening procedures will be documented in the appropriate study forms, including logs and case report forms. Clinical assessments and findings will also be documented as appropriate. No identifying information will be retained for women who do not enroll in the study.

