Second visit – The second visit window of ultrasound scan will be between 30–34 weeks of gestation. This will be applicable for all women who have had their first scan during 22–26 weeks of gestation as well as newly enrolled women during 30–34 weeks of gestational age. We have identified this window based on the antenatal care seeking in this setting, where the first point of contact of the pregnant woman with the health system is in the third trimester. The same procedures as described in the first visit will be done. However, at the second visit, cardiotocography (CTG) and umbilical artery continuous wave Doppler image through UmbiFlow device will also be obtained. All scans of a woman (whether 1 or 2) will be included in the model at the relevant gestational age time points. 

Follow up – We will obtain contact information (phone number) from all enrolled women. A trained research midwife will be responsible for making phone calls, as well as performing household visits for immediate and early identification of the pregnancy outcome. A hotline number and emergency transfer for delivery will be provided to the enrolled women. In case of live births, a team of CHWs will perform home visits to the baby at post-natal day 1 and 6. At the first visit, labor and delivery information including questions related to delayed cry, meconium passage and hospital course (if any) will be collected and the weight and length of the baby will be recorded. In subsequent visits, the baby will be examined by CHW for questions related to early neonatal sepsis on standardized questionnaires. Facilitated referral will be provided in case the mother or newborn requires treatment. In case of a stillbirth, the same labor and delivery information will be collected at day of outcome.

Please refer to
Figure 1 for the study flow diagram.

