**Figure 2. f2:**
[figure not shown]
Machine learning algorithm for this study.

Statistical analysis – Classical data analysis will be performed using
SPSS version 20.0. Data will be reported as percentages and means +/- standard deviation where appropriate. Pearson chi-square will be used to compare qualitative data between groups. A student's t-test or Mann Whitney U test (based on assumption of normality) will be used to compare data between groups with presence or absence of adverse perinatal outcomes. Associations between various Doppler and model-based parameters and adverse perinatal outcome will be analyzed by multiple logistic regression. Machine learning will be performed using the Multiple Kernel Learning approach developed in-house and described previously
^18^.

Ethical concerns – This study has been approved by AKU Ethics Review Committee (4872-Ped-ERC-17). Written informed consent will be obtained from each pregnant woman to ensure that the she is informed of and fully understands what will and may happen to her and her baby while participating in the research study. If the woman requests for additional time or indicates the need for consultation with other family members, she will be provided time, as long as she remains in the studies window period. Informed consent will be obtained by the research assistant at the center before any kind of study data is obtained. Fetal ultrasonography will require additional 15–20 minutes which may cause the woman some inconvenience. This will be clearly explained prior to recruitment. The patient will also hold the right of requesting discontinuation of scan. For any abnormal finding on fetal ultrasound or pregnancy related complication, the woman will be examined by the PHC physician. If there is need for hospital referral, facilitated referral will be done to the pregnant woman’s hospital of choice, which usually is Jinnah Postgraduate Medical Center which is a public tertiary level health center in Karachi. There will be no additional cost to the family for participation in this project.

The results of this study will be shared through newspaper articles in the local media, continuous medical education seminars, conference proceedings and publications in well reputed journals.

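### Low birth weight and prematurity are cuts of continuous measures, and no continuous-outcome analysis of birth weight or gestational age at birth is named beside them

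*Protocol article*

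**What the plan says.** Under Outcomes in the Study protocol section, the secondary outcomes include "LBW – Birth weight < 2.5 kg" and "Prematurity – Birth of a fetus < 37 weeks of gestation". Under Follow up, at the first home visit after a live birth, "the weight and length of the baby will be recorded". Gestational age at birth is not listed as a collected item, but the 37-week outcome cannot be assigned without it. The only dating method named is last menstrual period, under Recruitment.

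The Statistical analysis paragraph names chi-square for qualitative data. It also names a t-test or Mann-Whitney test that "will be used to compare data between groups with presence or absence of adverse perinatal outcomes". For the relation to the ultrasound measures it says: "Associations between various Doppler and model-based parameters and adverse perinatal outcome will be analyzed by multiple logistic regression". No model with a continuous outcome is named.

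Under Sample size estimation: "If 500 pregnant women are to be enrolled in the study duration, we expect to find approximately 25–30 adverse perinatal outcomes". The size of 500 rests on the stability of the machine learning. No power calculation for an association is given.

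**The concern.** Once birth weight is cut at 2.5 kg, a baby of 2.45 kg and one of 1.2 kg carry the same value, while babies of 2.45 kg and 2.55 kg carry opposite values. The same happens to gestational age around 37 weeks. If the association with a Doppler parameter runs along the whole scale, much of the evidence for it lies in differences that the cut removes.

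This is a proof-of-concept study of whether haemodynamic parameters carry prognostic signal. Its primary outcomes, stillbirth and early neonatal death, are binary by nature and few. Birth weight and gestational age at birth are available for most of the cohort as measurements. An association that 500 women could show on the full scale may be missed when only the cut is analysed.

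**Working it through.** **Inputs from the article.** Base size 500; 5% inflation; 30 stillbirths per 1000 total births; 30 neonatal deaths per 1000 live births; cut-offs 2.5 kg and 37 weeks.

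**Assumed, because the article gives no figure.** Prevalence *p* of each cut outcome, 15–35%; a normal outcome; a weak linear association with correlation *r* of 0.10, 0.12 or 0.15; two-sided 5% test.

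**The plan's own figures.** 500 × 1.05 = 525, as stated. Expected deaths: 500 × 0.03 = 15 stillbirths, leaving 485 live births; 485 × 0.03 = 14.6; total 29.6, within the stated 25–30. Both reproduce.

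**Information kept by the cut.** For a normal outcome cut at *z* = Φ⁻¹(*p*), the efficiency relative to the full scale is eff = φ(*z*)² / [*p*(1−*p*)]. At *p* = 0.25: *z* = −0.674, φ = 0.3178, eff = 0.1010 / 0.1875 = 0.539.

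| *p* | eff | loss | 500 women are worth |
|---|---|---|---|
| 15% | 0.426 | 57% | 213 |
| 20% | 0.490 | 51% | 245 |
| 25% | 0.539 | 46% | 269 |
| 30% | 0.576 | 42% | 288 |
| 35% | 0.603 | 40% | 302 |

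Outside that range, the loss is 66% at *p* = 10%. It reaches its minimum under normality, 36%, at *p* = 50%.

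**Power.** Full scale: Φ(√500·*r* − 1.96). Cut: Φ(√500·*r*·√eff − 1.96). At *r* = 0.12 and *p* = 25%, the full scale gives Φ(2.683 − 1.96) = 0.765 and the cut gives Φ(2.683 × 0.734 − 1.96) = 0.504.

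| *r* | full scale | cut, *p* = 15% to 35% |
|---|---|---|
| 0.10 | 0.61 | 0.31 to 0.41 |
| 0.12 | 0.765 | 0.42 to 0.55 |
| 0.15 | 0.92 | 0.59 to 0.74 |

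**Simulation.** With *n* = 500, *r* = 0.125 and 1500 replicates, linear against logistic regression gave losses of 60%, 47% and 43% at *p* = 15%, 25% and 33%, close to the formula. With a left-skewed outcome (an assumed reversed gamma, shape 3, as might suit gestational age) the losses were 76%, 64% and 53%.

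**The opposite case.** Suppose instead that the Doppler parameter is shifted by δ = 0.3 SD only in babies below the cut and is unrelated to the outcome elsewhere. Its correlation with the continuous outcome is then δφ(*z*)/√(1 + δ²*p*(1−*p*)) in absolute value, and with the binary outcome δ√[*p*(1−*p*)]/√(1 + δ²*p*(1−*p*)). At *p* = 15% these are 0.0695 and 0.1065. Power is Φ(22.36 × 0.0695 − 1.96) = 0.34 on the full scale and Φ(22.36 × 0.1065 − 1.96) = 0.66 for the cut. At *p* = 25% it is 0.56 against 0.82, and at *p* = 35% 0.69 against 0.89. The advantage reverses in this extreme case, where the boundary of the effect sits exactly at the cut.

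**The case against.** A reader might infer that the plan analyses these measures only as cuts and thereby throws away 40–57% of its information. The article does not support that, for four reasons.

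- **Exclusivity is inferred.** The statistics paragraph is short and sits in a journal article. It names no model for any single secondary outcome and does not exclude a continuous one. The machine-learning section relates clusters to clinical findings and outcome without limiting these to binary form.
- **The logistic sentence may not concern these outcomes.** Under Sample size estimation, the expected 25–30 adverse perinatal outcomes are derived from stillbirth and neonatal death rates alone. On that reading logistic regression suits the outcome, and the analysis of birth weight and gestational age is simply not described. The abstract and aim use the term more widely, so the scope is unclear. On either reading no continuous-outcome model is named.
- **The percentage is not the plan's.** It depends on assumed prevalence, normality and linearity. The Introduction describes absent or reversed flow in compromised fetuses, so an effect concentrated in the lower tail is plausible, and there the cut can be the stronger analysis.
- **The aim needs binary outcomes.** Identifying at-risk fetuses and comparing sensitivity and specificity with UmbiFlow both require them.

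All four points stand. They limit the claim and rule out replacing the cut-offs. They do not remove the case for adding continuous analyses of data that the study needs anyway. Data availability is a further limit: recording of weight is explicit for live births only, and gestational age at birth is implied, not listed.

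**Conclusion.** The point holds as a minor improvement to the secondary analyses. Two outcomes are defined as cuts of continuous quantities, the association methods named work on presence or absence, and no continuous-outcome model is named for either quantity.

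Under a roughly linear association, a normal outcome and 15–35% prevalence, analysing the cut alone would cost about 40–57% of the information. The cost may be larger for a skewed gestational age. It is smaller, or becomes a gain, if the effect lies wholly in the lower tail. Since the article establishes neither shape, the sound course is to run both analyses. The primary outcomes and the sample size are not affected.

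**What to change.** In the Statistical analysis paragraph, add linear regression with robust standard errors (or a rank-based method if the distribution is badly skewed) on the Doppler and model-based parameters for:

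1. birth weight in grams among live births, adjusted for gestational age; and
2. gestational age at birth.

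Keep the binary analyses of "LBW – Birth weight < 2.5 kg" and "Birth of a fetus < 37 weeks of gestation" beside these, for sensitivity, specificity and clinical reporting. List gestational age at birth as a collected item.

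The cost is a few more secondary analyses; no new visits are needed, and no measurement beyond what the 37-week rule already requires. Any adjustment or standardisation for gestational age inherits the error of dating by last menstrual period, which should be stated with the results.

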## Discussion

The study will start recruitment in March 2018. Training the machine learning algorithms with data generated from the computational model and validating it in a population at risk would enable to identify the fetus and placenta that maybe compromised and be at risk for higher perinatal morbidity and mortality. This data would allow screening of pregnant women to detect at- risk and high-risk pregnancies. Early detection of these pregnancies would allow for timely referral to improve outcomes. Please refer to
Figure 3 for the clinical decision making algorithm that may be proposed.

**Figure 3. f3:**
[figure not shown]
Proposed approach in the flow chart of clinical decision making.
